**Methods : Assignment of interventions**

Allocation:

A random block allocation sequence will be used to generate with a 1:1 ratio using a computer-generated randomization program by an independent party, who will not be involved in enrolling participants or assigning them to interventions.

Blinding: This study will be a non-blinding study.

**Methods: Data collection, management, and analysis**

We aim to gather all the information’s about the patient base line characteristics, the details of the IOL progress and the maternal and fetal outcomes.

To ensure accuracy and efficiency, we will utilize pre-printed forms to record this information in the medical files (Patient data form). Subsequently, we will enter the recorded data into an Excel spreadsheet, facilitating easy management and analysis.

Quantitative variables with are expressed as mean ± standard deviation (SD), Medians [1st Q- 3rd Q]. Qualitative variables are expressed as percentages. The statistical analysis was carried out using “XLSTAT 2022.3.2.1346”. Data were analyzed using Student-test, Mann-Whitney and Chi square. To compare the two groups, per-protocol analysis was employed. Kaplan-Meier survival analysis with a log-rank test was utilized to compare the primary outcome measure. ANCOVA-test analysis was performed to identify independent factors that may influence the time to APL. All statistical tests were two sided and were performed at a significance level of α=0.05.

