**Methods: Participants, interventions, and outcomes**

Study setting:

This trial will be conducted at the obstetrics and gynecology department of the university hospital Mongi Slim la Marsa, Tunis, Tunisia.

Study start date: February 8, 2021.

Participants’ eligibility criteria:

Inclusion criteria:

- Age ≥ 18 years old
- Full term (36 weeks and 3 days of gestation reached)
- Singleton gestation in cephalic presentation
- Bishop score of ≥ 6

Exclusion criteria:

- One or more previous caesarean scars (caesarean section, myomectomy with damage to the uterine cavity)
- Spontaneous rupture of membranes
- Spontaneous onset of labour
- Multiple pregnancies
- Malpresentation (breech, transverse or oblique presentations)
- Polyhydramnios
- Macrosomia (EFW ≥ 4000g)
- Narrow pelvic canal
- Severe foetal growth restriction (EFW ≤3^éme^ Percentile)
- Major foetal abnormalities
- Maternal infections: HIV infection, genital herpes, syphilis, hepatitis B or C
- COVID-19 infection
- Patient aged more than 40 years old
- Severe myopia
- Maternal cardiac disease
- Maternal fever
- Placenta previa
- Meconial amniotic liquid
- Patients declines to participate in the study

Interventions:

Each patient will receive comprehensive information regarding the study objective, and a reflection period will be allocated to facilitate the patient's informed decision-making process before granting their consent.

Prior to randomization, the investigator will conduct a double-check of patients' eligibility, and participants who meet the criteria will be sequentially assigned a study number.

Patients included in the study will be assigned to either early amniotomy (EA) or late amniotomy (LA) group:

In Group A (EA): Amniotomy will be performed soon after randomization, and oxytocin infusion will start 30 minutes later.

In Group B (LA): IOL will be initiated with oxytocin infusion, and amniotomy will be performed 4 hours later unless deemed necessary earlier (e.g. for non-reassuring fetal heart rate on the cardiotocography).

In case of impossibility of membrane rupture, the participant will be excluded.

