The oxytocin administration protocol will be implemented utilizing a syringe infusion pump for optimal delivery. The initial dose will be set at rate of 2mUI/min, and it will be increased by and additional 2mUI every 30 minutes. To ensure safety, the infusion rate will not exceed 42 mUI per minute. In case of hyperstimulation or abnormalities in the cardiotocography (CTG) readings, the oxytocin infusion will be halted or reduced accordingly.

The progress of labor will be regularly monitored, with continuous monitoring of the cardiotocography (CTG), cervical dilatation, maternal temperature and blood pressure. All findings and observations will be documented in the patient's medical records.

Once regular and painful contractions have been established, epidural analgesia will be presented as a potential option for pain management.

The monitoring of labor relies on a one-to-one care. Cervical examinations will be performed every 4 hours in the absence of uterine contractions. However, if the patient experienced the onset of labor, the examinations will be conducted hourly, and the midwife documents the findings.

In cases where instrumental deliveries will be required, Simpson type forceps will be utilized. 5 IU of synthetic oxytocin will be administered intravenously at the delivery of the baby's anterior shoulder.

The decision to perform a cesarean section will be made by the supervising team in consultation with the attending consultant and after obtaining the patient's consent.

Concerning the newborn examination, the following parameters will be documented: gender, birth weight, Apgar score at 1, 5, and 10 minutes after birth, as well as signs of post-maturity.

Additionally, any neonatal resuscitation, complications, their reasons, and the duration of admission to the neonatology department will be recorded.

The Apgar score will be used to evaluate the newborn's well-being at birth. A score of seven or less will indicate neonatal distress, while a score of three or less will indicate a state of apparent death, necessitating immediate life-saving measures.

Postpartum examination, complications, and estimated blood loss throughout the entire process will be documented.

Outcomes:

The primary outcome is the duration between initiating the oxytocin infusion and the start of the active phase of labor (APL) defined as cervical dilatation of 5 cm(12,13)(14).

The secondary outcomes are:

- Time to vaginal delivery (VD)
- Caesarean delivery rate

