- Intrapartum and postpartum fever (Chorioamnionitis, endometritis…)
- Postpartum haemorrhage (PPH)
- Apgar scores at 1 and 5 min
- Neonatal sepsis and newborn admission to the neonatal intensive care unit (NICU).

Participant timeline:

Sample size:

The sample size was calculated using power calculations to detect a significant reduction in the time to APL. Based on the previous IOL performed in the department, the mean time needed to reach APL was 7± 3 hours and 36 minutes. Using an alpha error of 0.05 and 90 % power, aiming to decrease by 150 min the time to APL in EA group, a minimum of 44 patients are needed in each arm(15). The target is to enroll 100 women.

Recruitment:

The study will be presented to all medical provider to enhance the best adhesion to the protocol. To maximize patient recruitment, women will be sensitized and educated about the indications and potential benefits of the study. Rigorous monitoring of outcomes and maintaining high standards will be prioritized to attract more patients.

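### The only group comparison is per protocol and women with failed membrane rupture are excluded after randomisation, so the groups analysed are not the groups randomised

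*Protocol*

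**What the plan says.** The section on data collection, management and analysis states: "To compare the two groups, per-protocol analysis was employed". No intention-to-treat or all-randomised analysis appears anywhere in the Protocol, and the per-protocol set is not defined.

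The Interventions text adds one explicit exclusion: "In case of impossibility of membrane rupture, the participant will be excluded". When it applies depends on the arm:

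- Early arm: "Amniotomy will be performed soon after randomization, and oxytocin infusion will start 30 minutes later".
- Late arm: oxytocin comes first, and "amniotomy will be performed 4 hours later unless deemed necessary earlier".

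The primary outcome is the time from the start of oxytocin to 5 cm dilatation, compared by Kaplan-Meier and a log-rank test. The allocation section says: "This study will be a non-blinding study". The sample-size text makes the aim one of superiority: "aiming to decrease by 150 min the time to APL in EA group".

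**The concern.** A superiority comparison is protected by randomisation only while every randomised woman is counted in her own arm. Two stated rules break that here.

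First, the failed-rupture exclusion acts after allocation. Every early-arm woman faces it before oxytocin has started. A late-arm woman normally faces it after about 4 hours of oxytocin, and only if her membranes are still intact. The women removed from the two arms are therefore selected at different stages of labour. If ease of rupture is related to how quickly labour progresses, which is plausible but not stated, the removals are related to the primary outcome and differ by arm.

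Second, per protocol is the sole basis of comparison but membership is undefined. The text does not say how a late-arm woman is classified if she ruptures spontaneously, reaches 5 cm or delivers before the 4-hour amniotomy. In an open-label trial, staff know the arm when they judge rupture impossible or a woman off protocol.

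At stake is whether a significant result can be attributed to the timing of amniotomy at all.

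**Working it through.** **Inputs (Protocol, Sample size and analysis sections).** Mean 7 h = 420 min; SD 3 h 36 min = 216 min; target difference 150 min; two-sided alpha 0.05; power 90%; 1:1 allocation; minimum 44 per arm; enrolment target 100, that is 50 per arm.

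**The plan's own figure.** n per arm = 2 × 216² × (1.960 + 1.282)² / 150² = 43.6, rounded up to 44. The stated sample size reproduces. It does not depend on which women are analysed.

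**Illustration A: late-arm women who reach 5 cm before 4 hours.** This assumes that they would be treated as off protocol, which the document does not say.

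Under a normal model, (240 − 420)/216 = −0.833, so P(T < 240) = 0.202. The mean of those remaining is 420 + 216 × φ(0.833)/(1 − 0.202) = 496 min. Gamma and lognormal models with the same mean and SD give:

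| Model | Share before 240 min | Late-arm mean if all are dropped | Shift |
|---|---|---|---|
| Normal | 20.2% | 496 min | 76 min |
| Gamma | 20.7% | 485 min | 65 min |
| Lognormal | 18.1% | 471 min | 51 min |

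That is about 10 of 50 late-arm women. The shift is 51/150 = 0.34 to 76/150 = 0.51 of the target difference, with no true effect.

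Null simulation of the log-rank test (gamma times, 50 per arm, no censoring, 5,000 trials per scenario):

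| Share of these women dropped | Rejection rate |
|---|---|
| None | 5.6%, nominal within simulation error and the approximation of the test |
| A quarter to a half | about 6–9% across runs |
| All | about 18%, nearly all in favour of early amniotomy |

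**Illustration B: failed rupture removed from the early arm only.** The Protocol gives no failure rate, so 2–10% is assumed. The extreme case is that the failures are exactly the slowest women. Under the normal model the fall in the early-arm mean is 216 × φ(z)/(1 − q), where z is the upper-q point:

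- q = 2%: 11 min
- q = 10%: 42 min

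Across the three models the range is about 11–53 min, which is a ceiling. The log-rank rejection rate with 10% removed depends on the link between failure and speed of labour:

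| Link to slow labour | Rejection rate |
|---|---|
| Unrelated | about 5.5% |
| Correlation 0.3 | about 7% |
| Correlation 0.6 | about 11% |
| Exactly the slowest | about 33% |

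**Power under the fix.** If the 150-min effect still holds with every woman included, 50 per arm gives 93.5% power (normal approximation). If exclusions left 40 per arm, power would be 87.4%, below the planned 90%.

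**The case against.** The strongest reply is that the late-arm figures rest on a rule the Protocol never states, and that the details of a per-protocol set commonly belong in the SAP, which is not at hand. Much of this stands as a limit on size. It does not remove the point, because the Protocol does not leave the population open: it fixes per protocol as the comparison and states an exclusion after randomisation.

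Four stronger readings are tempting and are not supported.

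- **That late-arm women given amniotomy before 4 hours for a worrying fetal trace are deviators, so that the safety comparison loses its highest-risk women.** The late-arm rule itself allows earlier amniotomy when deemed necessary. These women followed the protocol, and nothing in it removes them.
- **That reaching 5 cm before 4 hours is non-adherence.** Five centimetres is a dilatation threshold, not membrane rupture. An undelivered woman with intact membranes can still have the scheduled amniotomy. Illustration A is therefore conditional, and it is zero if none of these women are dropped.
- **That the bias favours early amniotomy in both arms.** The failed-rupture exclusion also applies to the late arm. A failure there at 4 hours may remove a slow woman, which would favour late amniotomy. The document does not say that rupture is easier after oxytocin.
- **That the false-positive rate is about 30%.** A t-test gives 30–31% in the extreme case of Illustration A, but the Protocol assigns the primary outcome to the log-rank test, which gives about 18%.

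Failed rupture may also be uncommon, since every woman enters with a Bishop score of at least 6. If it is rare or unrelated to speed of labour, that exclusion distorts little.

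**Conclusion.** The point holds. Per protocol is the only stated comparison, and the failed-rupture exclusion removes women after randomisation at different stages of labour in the two arms. The analysed groups are then not the randomised groups, and the comparison can be biased in an open-label superiority trial.

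The documents determine neither the size nor the direction of that bias. The range runs from essentially none, if no early-progressing late-arm women are dropped and failure is rare or unrelated to speed, to a spurious late-arm shift of one third to one half of the 150-min target and a log-rank false-positive rate of about 18%, if all late-arm women reaching 5 cm before 4 hours are dropped. These figures rest on the plan's 420 ± 216 min, on assumed distribution shapes (the rejection rates on a gamma shape), and on assumed rules for who is dropped. A plan whose undefined analysis set allows that whole range needs correcting before its result can be relied on.

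**What to change.** Three changes to the text:

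1. Make the primary analysis intention-to-treat: every randomised woman is analysed in her allocated arm, whatever happened to her membranes and whenever she reached 5 cm.
2. Replace the failed-rupture exclusion with a statement that the woman remains in follow-up and is analysed as randomised. This concerns data and analysis only, not her care.
3. Keep per protocol as a sensitivity analysis only, with membership defined in advance. The definition should state that late-arm amniotomy before 4 hours when deemed necessary is within protocol, and should say how spontaneous rupture, 5 cm or delivery before 4 hours is classified.

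The cost is small. Data collection continues in the women who would have been excluded, and the estimated effect may be somewhat smaller because women who did not receive the planned amniotomy are counted. The minimum of 44 per arm does not change.

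### Time to active labour is tested as a time-to-event outcome but modelled by ANCOVA, which has no value for women who never reach 5 cm

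*Protocol*

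**What the plan says.** All references are to the Protocol.

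- **Outcome** (Methods: Participants, interventions, and outcomes): the main endpoint is given as "the duration between initiating the oxytocin infusion and the start of the active phase of labor (APL) defined as cervical dilatation of 5 cm". Caesarean delivery rate is a secondary outcome.
- **Primary comparison** (Methods: Data collection, management, and analysis): "Kaplan-Meier survival analysis with a log-rank test was utilized to compare the primary outcome measure". No covariates or strata are named. "All statistical tests were two sided and were performed at a significance level of α=0.05".
- **Covariate model** (next sentence of the same section): "ANCOVA-test analysis was performed to identify independent factors that may influence the time to APL".
- **Planning figures** (Sample size): "the mean time needed to reach APL was 7± 3 hours and 36 minutes"; "aiming to decrease by 150 min the time to APL in EA group"; "Using an alpha error of 0.05 and 90 % power". The result is 44 per arm, with a target of 100 women in total.
- **Baseline information**: eligibility requires "Bishop score of ≥ 6", so the score must be assessed before entry. Baseline characteristics are to be collected but are not listed. Parity is not named, and no eligibility criterion restricts it.

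**The concern.** Two adjacent sentences treat one outcome in two ways that do not fit together. Kaplan-Meier and log-rank regard time to APL as a time that may be censored. ANCOVA regards it as a number measured on everyone, with roughly normal errors of constant spread.

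Caesarean delivery is a listed outcome, so it is foreseeable that some women will be delivered before 5 cm. They can contribute censored follow-up to the survival analysis but have no outcome for the ANCOVA. The factor analysis would then describe a different set of women from the primary comparison, or rest on times that were never observed.

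At stake is whether the factors reported as independent, and any arm effect read from that model, can be set beside the primary result.

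**Working it through.** **1. The plan's own figure.** Control mean 7 h = 420 min; SD 3 h 36 min = 216 min; difference 150 min; two-sided alpha 0.05; power 90%.

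n per arm = 2 × [216 × (1.960 + 1.282) / 150]² = 43.58, rounded up to 44. This matches the protocol. The formula uses one SD for both arms and implies an early-arm mean of 420 − 150 = 270 min.

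**2. Are normal errors plausible?**

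- Control arm: Φ(−420/216) = Φ(−1.94) = 2.6% below zero minutes.
- Early arm, SD unchanged at 216: Φ(−270/216) = Φ(−1.25) = 10.6% below zero.
- Early arm, SD shrinking in proportion to the mean: SD = 270 × 216/420 = 139 min, and the share below zero returns to 2.6%. The arms then have SDs of 216 and 139 min, and constant spread fails instead.
- A positive outcome with the control coefficient of variation (216/420 = 0.51) has skewness of about 1.0 if gamma and 1.7 if lognormal.

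These are marginal figures, not residuals after covariates. They make the assumption doubtful; they do not disprove it.

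**3. What does leaving out women without an APL time do?** The documents give neither a caesarean rate nor the share occurring before 5 cm, so both the share and the covariate's strength are assumed. The simulation used lognormal times with means 420 and 270, coefficient of variation 0.51 in both arms, 50 per arm, one baseline covariate explaining a share R² of the variance of log time, non-informative censoring and 1,500 replicates. ANCOVA used only women who reached APL. The true difference is −150 min.

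| R² | Not reaching APL | Mean ANCOVA difference (min) | Log-rank power | Adjusted Cox power |
|---|---|---|---|---|
| 0.1 | 0% | −150.0 | 98.5% | 99.1% |
| 0.1 | 8.6% | −145.9 | 98.4% | 99.2% |
| 0.1 | 17.0% | −137.3 | 98.1% | 98.7% |
| 0.3 | 0% | −150.7 | 98.5% | 99.8% |
| 0.3 | 8.5% | −144.1 | 98.1% | 99.7% |
| 0.3 | 17.2% | −137.1 | 96.9% | 99.3% |

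Shrinkage runs from (150 − 145.9)/150 = 2.7% to (150 − 137.1)/150 = 8.6%. Longer times are more often censored, and the control arm has more of them.

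**4. Is either test invalid?** With no true difference, the log-rank test rejected in 4.7 to 5.9% of replicates and the ANCOVA arm term in 4.1 to 5.5%. Neither is invalid under non-informative censoring. The adjusted Cox test rejected in 6.0 to 6.9%, so its power is slightly overstated here.

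**5. What would adjustment add?** At the planned effect, little (last two columns). At a smaller true difference of 80 min:

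- R² = 0.1: log-rank power 48 to 50%, adjusted Cox 52 to 55%.
- R² = 0.3: log-rank power 45 to 51%, adjusted Cox 60 to 68%.

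R² appears nowhere in the documents, so the gain cannot be derived from them.

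**The case against.** The case against is substantial, and much of it stands.

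- **The primary test is sound.** A reader might infer that an unadjusted log-rank test is wrong for a skewed time that some women never reach. It is not. Log-rank accommodates both features, and randomisation makes it valid without covariates. Adjustment or stratification is a matter of efficiency.
- **Power gains are easily misquoted.** Putting SD × √(1 − R²) into the t-test formula, with R² of 0.1 to 0.3, raises power at 44 per arm from 89.6% to 92.4–97.1%. Those figures belong to a normal-error comparison of means, not to log-rank or Cox. In Cox regression, adjustment does not reduce the standard error of the log hazard ratio. In a separate simulation without censoring (50 per arm, 600 replicates) it rose from 0.214 to 0.219 at R² = 0.1 and to 0.224 at R² = 0.3. Any gain comes from a larger conditional effect.
- **Strong baseline predictors are not documented.** Parity is not named as collected, and the Bishop score is cut off below 6, which narrows its range.
- **Bias from losing the slowest women is not shown.** The protocol does not say how women without an APL time enter the ANCOVA. Caesareans need not select slow labours, since the protocol also foresees cardiotocography abnormalities.
- **The ANCOVA is a search for factors**, not the stated treatment estimate, so its misfit does not touch the primary test. The medians and Mann-Whitney test listed beside it suggest that non-normality was expected. Covariates, transformations and handling of missing times may properly sit in an SAP that is not shown.

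What the objection does not remove is the choice of model. The protocol itself names ANCOVA for an outcome that it has just analysed as time-to-event.

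**Conclusion.** The point holds as a mismatch of models in a secondary analysis. ANCOVA cannot use women who never reach 5 cm, and its error assumptions are doubtful on the planning figures: 10.6% of the early arm below zero if the SD is unchanged, or clearly unequal SDs if it scales with the mean.

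The numerical consequence is modest under the assumptions tested: about 3 to 9% shrinkage of the arm difference if 8.5 to 17% of women never reach APL, with non-informative censoring. Caesarean before 5 cm is probably informative. That could distort both analyses more than shown here, and changing the model would not cure it.

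The documents support neither a criticism of the log-rank test nor a stated gain in power. That some women will not reach 5 cm, and that the times are skewed, are reasonable inferences rather than statements in the protocol.

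**What to change.** In Methods: Data collection, management, and analysis:

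- Replace the ANCOVA with a Cox or accelerated failure time model for time to APL, on the same women and with the same censoring rule as the Kaplan-Meier analysis.
- Pre-specify its terms: arm, baseline Bishop score and, if it is on the patient data form, parity.
- Report the adjusted treatment effect with its 95% CI as supportive, and label any search for further factors exploratory.
- Leave the unadjusted log-rank test as the primary comparison.

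The cost is wording, plus a check that parity is recorded. There is a small downside. An adjusted hazard ratio is a conditional effect and will not equal the unadjusted one, and Cox adds a proportional-hazards assumption. An accelerated failure time model avoids that assumption and gives a ratio of times, but a parametric version needs a chosen distribution.
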